#### 2.6.11. Covariates That Could Influence Adherence and Intervention Effects

At baseline, participant sociodemographic status and health history will be assessed. At all in-person data collection visits, mental health (symptoms of anxiety (Generalized Anxiety Disorder-7), stress (PSS), depression (Patient Health Questionnaire-8), body image (Body Shape Questionnaire), self-efficacy, disinhibited eating (Three-Factor Eating Questionnaire), and perceived social support) [43,60,61,62,63,64,65], sleep hygiene (Pittsburgh Sleep Quality Index) [66], and medication/supplement use will be determined. 

#### 2.6.12. Power and Sample Size 

This study is designed to evaluate the feasibility of the development of a larger study. The goal of the trial is to investigate and learn about data management, data collection methodologies, and how to design a larger study in the future. Forty-eight adults will be recruited, allowing for a 20% dropout rate, resulting in completed data collection on 40 individuals, which supports the calculation of confidence intervals for feasibility and effect size components. This feasibility-pilot study is not powered to detect statistically significant effects for improvement in chronic stress and body weight or the secondary/exploratory measures. The minimum detectable difference for these outcomes is 1 standard deviation based on the sample size in each of the four groups (n = 10/arm) between the baseline and post-intervention measurements that are correlated at r = 0.5, alpha = 0.05, and 80% power. We expect that there will be no change between baseline and post-intervention measurements in the control group. We did not consider power for the overall and multiple pairwise comparisons between different groups, nor will we correct for multiple comparisons because of the exploratory nature of the pilot study [67,68,69,70,71]. 

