Obesity is a modifiable risk factor for several cancers, including colorectal cancer [38]. Several studies have evaluated the effects of Mindfulness on eating behavior to support weight management. Stress-induced emotional eating is often associated with the consumption of “comfort foods” that tend to be more energy dense [39]. To determine the effect of Mindfulness on eating behavior, Fulwiler et al. used the “Three-Factor Eating Questionnaire”, an assessment that measures three aspects of eating behavior: cognitive restraint, uncontrolled eating, and emotional eating, to determine if emotional eating shifted in response to a Mindfulness intervention [40]. They presented the hypothesis that high levels of emotional eating could predict weight gain, while low levels of emotional eating could predict weight loss. They found in their study that Mindfulness was associated with reduced levels of emotional eating, but they failed to assess participant weight change [40]. A systematic review and meta-analysis conducted in 2019 evaluated 10 Mindfulness interventions on weight control and found a significant weight reduction among the Mindfulness participants when compared to control groups [41]. Therefore, Mindfulness may reduce emotional eating, energy intake, and weight gain, thus reducing the risk of colorectal cancer.

This paper describes the design of a TRE and Mindfulness intervention among young adults with obesity and CPS. Participants will be randomized to 8 weeks of TRE, Mindfulness, TRE and Mindfulness, or Control. The primary outcomes are related to feasibility and acceptability. Secondary outcomes are related to body weight, body composition, perceived stress, metabolites of the hypothalamic–pituitary–adrenal axis, circulating cardiometabolic disease risk markers, gut microbiome, and colonic inflammation. We hypothesize that the study will be feasible (i.e., recruit ≥ 50% of those approached, retain ≥ 80% of the participants, participants in the intervention groups will complete ≥ 80% of the intervention content, and all groups will complete ≥ 80% of planned assessments) and acceptable (i.e., based on a standardized acceptability survey by Pflugeisen et al. [42], that will be assessed during week 4 of the intervention and after completing the intervention). 

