#### 2.3.4. Randomization

Participants (*n* = 48) will be randomly assigned 1:1:1:1 to the following groups: (1) TRE; (2) Mindfulness; (3) TRE and Mindfulness; or (4) Control. We will use a stratified randomization approach considering sex (female vs. male) to ensure balance across treatment arms. Randomization will occur after all aspects of the baseline data collection are completed.

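### Section 2.6.12: 20% dropout from 48 leaves about 38 completers, not 40; the sentence needs restating, but the stated detectable difference of 1 SD survives rounding

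*Protocol article*

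**What the plan says.** Section 2.6.12 (Power and Sample Size) gives the number recruited, the dropout and the number of completers in one sentence: "Forty-eight adults will be recruited, allowing for a 20% dropout rate, resulting in completed data collection on 40 individuals". It adds that these completers support confidence intervals for feasibility and effect size components.

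The section then says "The minimum detectable difference for these outcomes is 1 standard deviation", "based on the sample size in each of the four groups (n = 10/arm"), for baseline to post-intervention measurements correlated at 0.5, with alpha 0.05 and 80% power. It also says that the study is not powered for stress, body weight or the secondary and exploratory measures.

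Two other places bear on the point. Section 2.3.4 says that the 48 participants "will be randomly assigned 1:1:1:1 to the following groups", which is 12 per arm. The Introduction lists among the feasibility hypotheses that the study will "retain ≥ 80% of the participants".

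**The concern.** The number recruited, the dropout rate and the number of completers are tied by one multiplication, and the stated values do not satisfy it. No other section reconciles them. The completer count feeds the per-arm number, and the per-arm number feeds the detectable difference, so an error in the first could carry through to the last. The article also says that the trial is meant to inform the design of a larger study, so its dropout arithmetic should be right.

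**Working it through.** **Inputs.** From Section 2.6.12: 48 recruited, 20% dropout, 40 completers, 10 per arm, detectable difference 1 SD, r = 0.5, alpha 0.05, power 80%. From Section 2.3.4: equal allocation, so 48/4 = 12 randomised per arm. The article does not say whether alpha is one- or two-sided. Two-sided is assumed here, because it reproduces the stated figure.

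**Completers.**
- At 20% dropout: 48 × (1 − 0.20) = 38.4, and per arm 12 × 0.80 = 9.6.
- Dropout implied by 40 completers: (48 − 40)/48 = 8/48 = 16.7%.
- Recruitment needed to expect 40 completers at 20% dropout: 40/0.80 = 50, or 52 with equal arms of 13.

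**The plan's own detectable difference.** The SD of the change is SD × √(2(1 − r)) = SD × √(2 × 0.5) = 1.0 SD. For a paired t-test in one arm, solve for the difference d (in SD) at which a noncentral t variable with n − 1 degrees of freedom and noncentrality d√n exceeds the two-sided 5% critical value with probability 0.80. At n = 10 this gives d = 0.996, which reproduces the stated 1 SD. Other calculations at n = 10 do not: one-sided paired t 0.85 SD, normal approximation 0.89 SD, two-sample comparison of changes 1.32 SD. The stated figure is therefore a within-arm, pre-post figure.

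**The same calculation at the arm sizes that 20% dropout gives** (non-integer n stands for an average):

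| Completers per arm | Detectable difference (SD) | Power at 1 SD |
|---|---|---|
| 10 (as stated) | 0.996 | 80.3% |
| 9.6 (38.4 in all) | 1.02 | 78.2% |
| 9.5 (38 in all) | 1.03 | 77.7% |
| 9 (the smaller arms if 38 split 10/10/9/9) | 1.07 | 74.8% |

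**Precision of a rate.** For a rate of 80%, the 95% half-width by the normal approximation is 1.96 × √(0.8 × 0.2/n): 12.4 percentage points with n = 40 and 12.7 with n = 38.

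**Retention criterion.** A 20% loss is the same as 80% retained, so the dropout allowance and the criterion agree. In whole people, 39/48 = 81.3% meets the criterion and 38/48 = 79.2% does not.

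**The case against.** The strongest objection is that this amounts to a copy-edit. The gap is about two people, the detectable difference is stated without decimals and still rounds to 1 SD, and the study disclaims power for these outcomes. Section 2.7 adds that no efficacy conclusions will be drawn. It takes the feasibility and acceptability rates over participants approached, so 38 or 40 completers is not their stated denominator. All of this stands, and it limits the size of the point. It does not make the sentence correct, because 38.4 does not round to 40.

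Four stronger readings are tempting, and the documents do not support them.

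- *A reader might infer that the stated detectable difference is not delivered.* The table shows 1.02 SD on average and 1.07 SD in an arm of 9, both 1 SD at the precision given.
- *A reader might infer that 48 came from the wrong inflation, 40 × 1.2 = 48, in place of 40/0.80 = 50.* That fits, but so does rounding per arm: 12 × 0.80 = 9.6, rounded up to 10, times 4 = 40. The article shows no derivation, so the origin is unknown.
- *A reader might infer a clash with the retention criterion, since 38 of 48 fails it.* But 38/48 is a loss of 10/48 = 20.8%, more than the allowance. The failure comes only from rounding 38.4 down.
- *A reader might infer that 50 or 52 participants are needed.* Nothing in this pilot depends on having exactly 40 completers.

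**Conclusion.** The point holds as a minor arithmetic correction. With 48 recruited, either the dropout is 20% and about 38 complete (9.6 per arm on average), or 40 complete and the dropout is about 17%. The discrepancy is 1.6 to 2 completers. At the stated dropout, the within-arm detectable difference rises by about 0.03 SD on average and 0.07 SD in an arm of 9. Power at 1 SD falls by about 2 percentage points on average, and by about 5.5 points (80.3% to 74.8%) in an arm of 9. No primary feasibility conclusion changes.

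The detectable-difference figures assume a two-sided paired t-test within an arm and the article's r = 0.5. The completer count needs no assumption beyond the stated figures.

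**What to change.** Keep 48 recruited and restate the sentence in Section 2.6.12 in one of two ways:

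- 20% dropout, about 38 completers (9 to 10 per arm), within-arm pre-post detectable difference about 1.0 SD (1.02 SD at 9.6 per arm, up to 1.07 SD in an arm of 9); or
- about 17% dropout (8 of 48), 40 completers (10 per arm), with the detectable difference left at 1 SD.

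Under the first option, change the per-arm number in the detectable-difference sentence to match. Leave the 80% retention criterion as it is under either option. The cost is a small edit within one section, with no extra participants and no change to design or analysis.

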#### 2.6.13. Data Management 

A large majority of data will be recorded directly or later uploaded into REDCap (version 14.1.3) [72], which is a secure web-based platform for building and managing online research-related databases and surveys.

### 2.7. Data Analytic Plan

Data will be managed using REDCap [72] and analyzed using the statistical software SAS (version 9.4, SAS Institute, Cary, NC, USA). The data will be organized and stored on an encrypted server. Metadata will be available and stored in an electronic lab notebook, including details of what, where, when, why, and how data were collected and processed. 

We will summarize feasibility and acceptability metrics using descriptive statistics such as frequencies, percentages, means, and standard deviations. The results will include the recruitment rate among eligible individuals approached, adherence (i.e., % interaction with asynchronous sessions, % of days adherent to the TRE protocol), % retained through post-intervention, and scores on the acceptability survey. The feasibility and acceptability rates will be estimated as the number of feasibility and acceptability participants divided by the total number of approached participants, respectively. A 95% confidence interval for the feasibility and acceptability rates will be calculated assuming a binomial distribution. Fisher’s exact test will be used to test whether feasibility and acceptability rates are significantly higher than their threshold rates (50% or 80%), respectively. A chi-square test will be used to test its relationship with other categorical clinical factors, and a *t*-test will be used for its relationship with other continuous clinical factors instead. Adjusted logistic regression (binary outcomes) or generalized linear models (GLM) (continuous outcomes) will be employed in multivariate analyses to assess their relationship with each other as clinical factors. 

Exploratory inferential statistics will be conducted, but no conclusions on the efficacy of the interventions will be drawn from the results. Initially, we will evaluate distributions, identify any outliers, and look for patterns of missing data. The continuous endpoints (stress, body weight, body composition, and cardiometabolic health) will be estimated among each of the groups, and the 95% confidence interval will be constructed assuming normal distribution, respectively. Then, a two-sample *t*-test will be utilized to compare each of the three intervention groups and the control group. GLM will be employed to estimate the adjusted difference in each of the continuous endpoints between the different groups. We will also investigate co-primary (body, weight, objective stress markers) and secondary outcomes (i.e., body composition, PSS, cardiometabolic measures) for between- and within-treatment differences and test for (treatment) × (time) interactions to compare the trends over time using generalized linear mixed models. We will investigate changes in microbial community diversity and composition (ASVs), tryptophan-related metabolites, and systemic and intestinal inflammation changes from baseline to post-intervention by treatment arm. The other binary endpoints will be compared between the different groups using Fisher’s exact test or chi-square test, respectively. Multivariate logistic regression will be further employed to compare these binary endpoints between the different groups, after adjusting for plausible confounders. Odds ratios and 95% confidence intervals will be calculated to evaluate the strength of any association that emerges.

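### Section 2.7 puts every tested feasibility and acceptability rate over the number approached, which fits only recruitment and contradicts the bases set in the Introduction

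*Protocol article*

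**What the plan says.** The Introduction of the protocol article names feasibility and acceptability as the primary outcomes and gives each feasibility criterion its own base:

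- Recruitment and retention: "recruit ≥ 50% of those approached, retain ≥ 80% of the participants".
- Content: "participants in the intervention groups will complete ≥ 80% of the intervention content".
- Assessments: "all groups will complete ≥ 80% of planned assessments".
- Acceptability is judged "based on a standardized acceptability survey", with no numeric cut-off in that section.

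Section 2.7 first lists the metrics to be summarised. Among them is "the recruitment rate among eligible individuals approached". Adherence and retention percentages follow without a stated denominator. The section then defines the feasibility and acceptability rates as the number of "feasibility and acceptability participants divided by the total number of approached participants". The next two sentences build on that definition: "A 95% confidence interval for the feasibility and acceptability rates will be calculated assuming a binomial distribution", and a test of "whether feasibility and acceptability rates are significantly higher than their threshold rates (50% or 80%), respectively".

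**The concern.** The only rate definition that carries the interval and the threshold test uses everyone approached as its denominator. People who were approached but never enrolled cannot be retained, attend an assessment or receive the intervention. Counting them in the denominator turns a retention rate into the product of recruitment and retention, which is then compared with a threshold meant for retention alone.

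The Introduction and section 2.7 therefore give different answers for the same primary outcome. A pilot that reaches its recruitment target exactly and keeps every participant would miss the retention criterion under section 2.7 and meet it under the Introduction. The article disclaims efficacy conclusions, so these rates are the main result handed on to the planners of the larger trial.

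**Working it through.** **Inputs.** Planned enrolment is 48, with 20% dropout allowed for and 40 completers (section 2.6.12). Allocation is 1:1:1:1 (section 2.3.4), so 12 per arm and 36 in the three intervention arms. The recruitment target is 50% and the retention target 80% (Introduction). The number approached, A, is not stated. I take A = 48 / recruitment rate and let recruitment run from the 50% target to 100%, so A runs from 96 down to 48.

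**The plan's own figure.** 40 × 1.20 = 48 reproduces the stated enrolment. Dividing instead gives 40 / 0.80 = 50, and 48 × 0.80 = 38.4. The differences are at most two people and do not affect this point. I use the stated 40 completers.

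**Retention over those approached.** The rate is retained / A = (retained / 48) × (48 / A), that is, retention × recruitment. Its ceiling, with nobody lost, is the recruitment rate.

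| Recruitment | Approached (A) | All 48 retained | 40 retained |
|---|---|---|---|
| 50% | 96 | 48/96 = 50.0% | 40/96 = 41.7% |
| 60% | 80 | 48/80 = 60.0% | 40/80 = 50.0% |
| 80% | 60 | 48/60 = 80.0% | 40/60 = 66.7% |
| 100% | 48 | 48/48 = 100% | 40/48 = 83.3% |

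At the 50% target the exact 95% intervals are 39.6% to 60.4% for 48/96 and 31.7% to 52.2% for 40/96. Both lie wholly below 80%.

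**When 80% becomes reachable.** With no dropout, 48/A ≥ 0.80 requires A ≤ 48/0.80 = 60, which is recruitment of at least 80%. With the planned 40 completers, A ≤ 40/0.80 = 50, which is recruitment of at least 48/50 = 96%.

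**Retention over those randomised.** 40/48 = 83.3%, exact (Clopper-Pearson) 95% CI 69.8% to 92.5%. This meets the Introduction's 80% as a point criterion.

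**The threshold test on the corrected denominator.** Section 2.7 asks for more than a point estimate: it tests for a rate significantly above the threshold. The one-sided exact binomial probability of 40 or more out of 48, when the true rate is 80%, is 0.36. The smallest count that clears one-sided 0.025 is 44/48 = 91.7% (p = 0.025, or 0.0248 unrounded). Correcting the denominator removes the artificial failure, but the planned result would still not pass the test.

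**The case against.** The strongest reply is that this is one loose sentence. Just before it, section 2.7 lists the metrics separately, and several of them have natural denominators: sessions for interaction, days for eating-window adherence, enrolled people for retention. That stands in part. Content completion and adherence can be read as percentages of sessions or days. A reader might infer that content completion is capped at 36/48 = 75% even with full recruitment, but that holds only if it is counted as people over everyone approached, and the text does not force that reading. For retention the reply fails. The list gives no denominator, and the only defined rate that feeds the interval and the test is the one over those approached.

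Other stronger readings are tempting and not supported:

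- *That the 80% criteria cannot be met even in a perfect trial.* Full recruitment with full retention gives 48/48 = 100%. The failure depends on the recruitment rate.
- *That this misfires a formal stop-or-proceed rule.* The article states hypotheses and says the results will inform a larger trial. It sets no progression rule.
- *That the two recruitment wordings clearly conflict.* Section 2.2 has only people who pass the online survey being phoned and invited, so those approached and the eligible people approached are plausibly the same group. Common wording would be tidier, but this is not a demonstrated contradiction.
- *That acceptability concerns only the 36 in the intervention arms, at 80%.* The article does not say who takes the survey, and 80% for acceptability is only implied by the pair of thresholds in section 2.7.
- *That the plan rules out results by arm.* It does not. Tabulation by arm is detail that an article may leave to other documents.

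It could also be said that an article condenses its protocol. That excuses omissions. It does not excuse a stated rule that contradicts another section.

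**Conclusion.** The point holds in a conditional form. Section 2.7 states one denominator for the tested rates. It suits recruitment only, and it contradicts the bases in the Introduction, most plainly for retention. If recruitment is at its 50% target, the retention rate as defined cannot exceed 50%, and the planned 40 completers give 42% where the rate among those randomised is 83%. The choice of denominator alone changes whether the 80% criterion is met.

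The size rests on an assumed 96 approached. The gap narrows as recruitment rises and disappears at 100%. Because the rule defines a primary outcome and is cheap to correct, it should be corrected before the rates are calculated.

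**What to change.** Replace the single-denominator sentence in section 2.7 with one denominator per criterion:

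- **Recruitment:** randomised / eligible individuals approached, in the same words in the Introduction and section 2.7.
- **Retention and assessment completion:** completed / randomised.
- **Content completion:** among participants randomised to the arms that receive that content.
- **Acceptability:** among randomised participants who are to receive the acceptability survey, stating who they are.

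Give each proportion an exact binomial interval. State also whether a criterion is met by the point estimate, as the Introduction implies, or only by a rate significantly above the threshold, as section 2.7 implies. For retention the two differ: 40/48 satisfies the first and not the second.

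The cost is wording. No new data, participants or visits are needed, provided the number of eligible people approached is logged, which the recruitment rate already requires.

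### The participant-count rate, binomial interval and threshold test do not estimate the two feasibility criteria stated as amounts completed (content and planned assessments)

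*Protocol article*

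**What the plan says.** The feasibility hypothesis at the end of the Introduction has four parts. Two are settled once per person: "recruit ≥ 50% of those approached, retain ≥ 80% of the participants". The other two are amounts of material: "participants in the intervention groups will complete ≥ 80% of the intervention content, and all groups will complete ≥ 80% of planned assessments".

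Section 2.7 (Data Analytic Plan) fixes one estimator for feasibility and acceptability: "The feasibility and acceptability rates will be estimated as the number of feasibility and acceptability participants divided by the total number of approached participants". It then adds that "A 95% confidence interval for the feasibility and acceptability rates will be calculated assuming a binomial distribution", followed by a test of whether the rates exceed their thresholds of 50% or 80%.

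Earlier in the same paragraph, means and standard deviations are among the planned summaries. The adherence results are listed there as percentages, among them "interaction with asynchronous sessions, % of days adherent to the TRE protocol". Section 2.4.2 sets 30 Mindfulness lessons per participant. Section 2.7 does not say what makes someone a feasibility participant for content or assessments.

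**The concern.** A binomial rate needs one yes or no per unit. Recruited and retained are of that kind. The percentage of content completed and the percentage of assessments completed are not: each person contributes a fraction. To apply the planned rule, each fraction must first be turned into a yes or no, and the rate then becomes the share of people above a cut-off. Comparing that share with 80% asks whether at least four in five people did enough. The Introduction, read as an amount, asks whether 80% of the material was completed.

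Feasibility is a primary outcome and is meant to inform a larger trial. If the stated analysis does not estimate the stated criterion, the same data can be reported as meeting it or missing it, depending on who does the conversion.

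**Working it through.** **The plan's own figure.** The document gives no interval width or power for feasibility, so there is none to reproduce. Its only power figure is the 1 SD detectable change in section 2.6.12, which concerns other outcomes.

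**Inputs from the document.**
- 48 participants, 1:1:1:1 (section 2.1), so 12 per arm.
- Two arms receive the lessons: 2 × 12 = 24 people.
- Lessons per person: 4 × 7 + 2 = 30 (section 2.4.2), so 24 × 30 = 720 in all.
- 80% of 30 lessons is 24.

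The lessons stand in for content here. The TRE arms also have dietitian sessions.

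**Step 1: one data set, two answers.** Suppose 18 people complete 30 lessons and 6 complete 12.
- Mean completion: (18 × 30 + 6 × 12)/720 = 612/720 = 85%, which meets 80%.
- Share of participants with at least 24 lessons: 18/24 = 75%, which misses 80%.

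The reverse is also possible. Suppose 20 people complete 24 lessons and 4 complete 6.
- Mean completion: (20 × 24 + 4 × 6)/720 = 504/720 = 70%, which misses.
- Share: 20/24 = 83%, which meets.

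**Step 2: how often this happens.** The spread of completion between people is not in the document. I assumed a beta-binomial model with within-person correlation (ICC) 0.1, 0.3 and 0.5, 24 people and 30 lessons, and simulated two verdicts: mean completion at least 80%, and at least 80% of participants at or above 80%.

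| True mean completion | Verdicts disagree (range over ICC 0.1 to 0.5) |
|---|---|
| 85% | about 51% to 74% of trials |
| 90% | about 22% to 37% |
| 95% | about 1% to 4% |

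At 85%, the mean meets 80% in about 83% to 97% of trials, while the participant share does so in about 22% to 32%. The reason is that only about 74% to 77% of individuals reach 80% when the mean is 85%.

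**Step 3: the formal test.** With n = 24, an exact one-sided 5% test that the share exceeds 80% needs 23 successes: P(X ≥ 23 | 24, 0.8) = 0.033, whereas P(X ≥ 22) = 0.115. So 23/24 = 96% of people would have to pass the cut-off. The document does not give the level or sidedness of its test, so 5% one-sided is an assumption.

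**The case against.** The best defence is that the Introduction can be read person by person: each participant in the intervention groups completes at least 80%. Every participant is then a yes or no, and a binomial on participants is valid; 19 of 24, for example, gives an exact 95% interval of 57.8% to 92.9%. This reading is fair, but it leaves the criterion incomplete, because the Introduction names no share of participants that must succeed on content or assessments.

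Section 2.7 also already lists means and standard deviations, which is part of what is needed for the percentage metrics. That stands for description. It does not change the fact that the interval and threshold test are attached to a participant count.

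Three stronger readings are tempting and should not be adopted.
- A reader might infer that lessons or days will be pooled as independent binomial trials, giving intervals that are too narrow. Section 2.7 counts people and nowhere plans pooling, so the document does not support that.
- A reader might treat the percentage of TRE-adherent days as a further failed criterion. It carries no threshold and is listed as an adherence result.
- A reader might say the result decides whether a larger trial proceeds. The document has no go/no-go rule; the pilot is meant to inform later work.

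**Conclusion.** The point holds as a mismatch between criterion and analysis. For two of the four primary feasibility criteria, the rule in section 2.7, followed as written, estimates the share of participants passing an undefined cut-off instead of the amount completed. Recruitment and retention are unaffected by this point.

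That the verdict can reverse follows from arithmetic alone. How often it would do so depends on the assumed beta-binomial model, the ICC range and the use of lessons as the content. On those assumptions the disagreement is large near 85% completion and almost vanishes by 95%. The choice of denominator and of one-sample test are separate matters; settling them would still leave the unit undefined. This should be corrected before analysis, and wording is enough.

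**What to change.** In section 2.7, keep the binomial interval, computed exactly, for recruitment and retention. For content and planned assessments, compute one percentage per participant among those assigned that content or those assessments. Report the mean with a 95% confidence interval based on variation between participants (t interval or participant-level bootstrap), and compare the mean with 80%.

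Alternatively, if a count of people is what the investigators want, reword the Introduction so that at least x% of participants complete at least 80%, with x stated, and apply the binomial to that count.

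The percentage of TRE-adherent days can be summarised per participant in the same way, as a descriptive result without a threshold. One clause should say that lessons and days are not to be treated as independent trials.

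The cost is one or two sentences and no new data. The two completion criteria would then carry a participant-level interval.

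### Fisher's exact test cannot compare one observed rate with a fixed 50% or 80% threshold, and the plan does not say whether that test or the observed-rate criterion defines feasibility

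*Protocol article*

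**What the plan says.** The Introduction of the protocol article makes feasibility and acceptability the primary outcomes. It expresses the feasibility hypothesis as observed rates: "recruit ≥ 50% of those approached, retain ≥ 80% of the participants", with intervention groups completing at least 80% of content, and "all groups will complete ≥ 80% of planned assessments".

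Section 2.7 (Data Analytic Plan) first plans a one-sample interval: "A 95% confidence interval for the feasibility and acceptability rates will be calculated assuming a binomial distribution". The next sentence assigns a test to the same rates. Fisher's "exact test will be used to test whether feasibility and acceptability rates are significantly higher than their threshold rates (50% or 80"%). No significance level or sidedness is given for it.

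Section 2.6.12 (Power and Sample Size) states: "Forty-eight adults will be recruited, allowing for a 20% dropout rate, resulting in completed data collection on 40 individuals". It says that this number supports confidence intervals for feasibility, and it gives no power for a test against a threshold.

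**The concern.** There are two problems.

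1. **The named test does not fit the question.** Fisher's exact test conditions on the margins of a 2×2 table formed by two observed groups. Here there is one observed proportion and a constant. The test can be run only by adding a second, fictitious group at the threshold rate. The plan does not define such a group, and its arbitrary size would drive the p-value. The sentence is not shorthand for a comparison between arms, because section 2.7 assigns Fisher's or chi-square tests to between-group comparisons of other binary endpoints separately.

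2. **There are two standards for the same rates.** The Introduction asks for an observed rate at or above the threshold. Section 2.7 tests whether the rate is significantly above it. The second is harder to meet, and the plan does not say how the two relate.

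At stake is how the primary result is read. The trial exists to inform a larger one, and a retention figure near the plan's own target would meet the first standard and not the second.

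**Working it through.** **Inputs.** N = 48, 20% dropout allowance and 40 completers (section 2.6.12). Thresholds of 50% and 80% (Introduction and section 2.7). Assumptions: retention is counted out of the 48 randomised, and the test is one-sided upper, as the words *significantly higher* suggest, at 0.05 or 0.025.

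**The plan's own figures.** 40 × 1.20 = 48 reproduces the recruitment number. A 20% loss from 48 leaves 48 × 0.80 = 38.4, while 40/48 = 83.3%. The planning allowance therefore corresponds to retention of 80% to 83.3%, and both ends are carried below.

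**Step 1: a valid test against 80%.** With X ~ Binomial(48, 0.80), the one-sided exact p-value is P(X ≥ x).

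| Retained | Observed rate | Exact p | At least 80% observed? | Significantly above 80%? |
|---|---|---|---|---|
| 39/48 | 81.3% | 0.500 | yes | no |
| 40/48 | 83.3% | 0.358 | yes | no |
| 43/48 | 89.6% | 0.062 | yes | no |
| 44/48 | 91.7% | 0.0248 | yes | yes |

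The cut-off of 44 is the same at one-sided 0.05 and 0.025. The smallest count meeting the observed criterion is 39, because 38/48 = 79.2%. From 39 to 43 retained, the two standards disagree.

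**Step 2: the planned interval.** The exact (Clopper-Pearson) 95% limits are the Beta(x, n − x + 1) quantile at 0.025 and the Beta(x + 1, n − x) quantile at 0.975. For 40/48 they are 69.8% and 92.5%. The lower limit is 77.3% for 43/48 and 80.02% for 44/48. In exact form, the interval already planned gives the same cut-off as the one-sample test.

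**Step 3: Fisher's test on 44/48 against an invented 80% group (one-sided).**

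| Invented group | p |
|---|---|
| 8/10 | 0.274 |
| 38/48 | 0.073 |
| 80/100 | 0.055 |
| 800/1000 | 0.028 |
| One-sample exact binomial | 0.0248 |

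The data are identical in every row. Only the size of the fictitious group changes, and p approaches the binomial value as that group grows.

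**Step 4: chance of meeting each standard (retention, n = 48).**

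| True retention | Observed rate at least 80% (X ≥ 39) | Significant (X ≥ 44) |
|---|---|---|
| 70% | 5.7% | 0.03% |
| 80% | 50.0% | 2.5% |
| 83.3% | 72.9% | 8.0% |
| 90% | 98.1% | 46.9% |

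**Step 5: other rates.** The number approached for recruitment is not given, so these are illustrations. 48/96 = 50% meets the observed criterion with exact p = 0.54 against 50%; 48/80 = 60% gives p = 0.046. If an 80% threshold were tested within one arm of 12, even 12/12 would give p = 0.80^12 = 0.069.

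**The case against.** The strongest reply is that the harm is small. The sentence before the test already plans a one-sample binomial interval, the metrics are also summarised descriptively, and section 2.6.12 rests the sample size on confidence intervals. This stands in part: the rates and a suitable interval will be reported whatever happens to the test. It does not rescue the test, which is named for the primary outcome and cannot be carried out as described. Nor does the pilot status cover it. The statement in section 2.6.12 that the study is not powered concerns stress, body weight and the secondary and exploratory measures, and the caveat in section 2.7 concerns efficacy conclusions.

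Three stronger readings are tempting, and the documents do not support them.

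- **That the test contradicts the planned dropout.** A reader might infer that true retention sits at the null value, so that the trial is set up to fail. But "allowing for a 20% dropout rate" is a planning allowance, not a forecast. The low pass rates are conditional on retention being that low.
- **That the primary conclusion turns on the p-value.** Section 2.7 does not say that feasibility is declared only on significance, or that a non-significant result means not feasible. The two standards differ in strictness and their relation is unstated. That is an ambiguity, not a proven contradiction.
- **That Fisher's test has a particular cut-off or power here.** Any such figure belongs to whichever reference group is invented, and the plan proposes none. Step 3 shows only that the result is arbitrary.

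**Conclusion.** The choice of test is wrong as written, for every threshold: Fisher's exact test does not compare a single rate with a constant. This conclusion needs no assumption.

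The second part is an unresolved ambiguity about which standard governs. Its size can be worked out only for retention, assuming n = 48 as denominator and a one-sided test at 0.05 or 0.025. The gap then runs from 39 to 43 retained and includes the plan's own 40 completers. A valid test would pass 2.5% to 8.0% of the time if retention were at the planning allowance, and 47% of the time at a true 90%.

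The denominator is a real assumption, because section 2.7 describes the feasibility and acceptability rates as divided by the number approached, which the article does not give. The comparison with the dropout allowance applies to retention only, not to recruitment against 50%.

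**What to change.** In section 2.7:

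1. Replace Fisher's exact test, for this use only, with a one-sample exact binomial test, and state its significance level and sidedness.
2. State that the observed-rate thresholds in the Introduction are the feasibility criterion. For retention out of 48, this means at least 39.
3. Report each rate with the binomial 95% interval already planned, specified as exact (Clopper-Pearson).
4. Label the p-value descriptive, and note that for retention it falls below 0.05 only from 44/48.

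The cost is a few sentences and one line of SAS code, with no change to data collection or sample size. The trade-off should be acknowledged: no significance claim is made for feasibility, and the observed-rate rule is lenient at the boundary. It passes 98% of the time at a true 90% and 6% at 70%, but 50% at exactly 80%. The interval reported beside it shows that uncertainty.
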